## 8.3 Protocol Deviations

A summary will be provided for all key protocol deviations by deviation sub-category and treatment group based on the FAS will be presented for Part A and Part A + B separately.

In addition, all protocol deviations will be listed and protocol deviations occurring due to the COVID-19 pandemic will be listed separately for FAS.

## 8.4 Demographics and Baseline Characteristics

All demographic and baseline characteristics data will be listed and summarized for Part A by treatment group using the FAS. Inferential statistical analysis of demographic or baseline data will not be performed.

### 8.4.1 Demographics

Continuous variables such as age (years) at screening collected on the case report form (CRF), height (cm), weight (kg) and BMI (kg/m^2) will be summarized using descriptive statistics.

Categorical variables such as age categories (18-64, 65-84, >84), sex, ethnicity and race will be

summarized using counts and percentages.

Childbearing potential status, contraception methods used and reason for non-child-bearing potential status for female participants will be provided in the listing only.

#### **8.4.2 Baseline and Disease Characteristics**

The following variables will be summarized:

- Drug and alcohol history;
- Smoking history;
- PsA medical history;
  - Duration of PsA (Year)
  - Duration of PsA symptoms (Year)
  - Current active psoriasis (yes/no)
  - [REDACTED]
  - [REDACTED]
- Geographic region: North America, Western Europe and Eastern Europe;
- Number of prior biologic agents (0;1;2);
- Concomitant methotrexate use (yes/no);
- Concomitant non-biologic disease-modifying anti-rheumatic drug (DMARD) at baseline (yes/no);
- Concomitant corticosteroids at baseline (yes/no);
- Baseline BSA;
- Baseline BSA  $\geq 3$  (yes/no);
- Baseline TJC68 count;
- Baseline SJC66 count;
- Baseline PASI (in patients with BSA  $\geq 3$ );
- Baseline PtAAP;
- [REDACTED]
- Baseline PtGADA;
- Baseline PhGADA;
- Baseline HAQ-DI;
- Baseline (PsAID)-12;
- Baseline BASDAI score;
- Baseline hs-CRP;
- Baseline hs-CRP  $\geq 6$  mg/L (yes/no);
- Baseline hs-CRP  $> 5$  mg/L (yes/no);
- Baseline ESR;
- Baseline DAPSA;
- Baseline mNAPSI score (in patients with baseline mNAPSI  $\geq 0$ );
- Presence of enthesitis at baseline (yes/no) [based on LEI];
- Baseline LEI score (in patients with baseline LEI  $\geq 0$ );

- Presence of enthesitis at baseline (yes/no) [based on SPARCC];
- Baseline SPARCC (in patients with baseline SPARCC  $\geq 0$ );
- Presence of dactylitis at baseline (yes/no);
- Baseline LDI (in patients with dactylitis);
- SF-36 PCS score
- Evidence of erosions on hands or feet in patients with a prior x-ray (yes/no);
- Evidence of juxta-articular bone formation on hands or feet in patients with a prior x-ray (yes/no)
- Baseline FACIT-fatigue

Continuous variables will be summarized using descriptive statistics and categorical variables will be summarized using counts and percentages. Percentage calculations will be based on the number of participants in FAS including participants with missing value in each treatment group.

### 8.4.3 Medical History

Medical history will be summarized by system organ class (SOC) and preferred term (PT) coded using Medical Dictionary for Regulatory Affairs® (MedDRA) Version 25.0 or higher. Counts and percentages will be presented by treatment group using the SAF.

### 8.4.4 Psoriatic Arthritis Previous Therapies

PsA previous therapies will be summarised by treatment group using the SAF using the following group terms with the individual drug names summarised within the group terms:

- anti-TNF biologics,
- anti-IL-17 biologicals,
- anti-IL23 biologicals
- other biologics coded by World Health Organization Drug Dictionary Enhanced (WHODDE)
- NSAIDs/COX-2 inhibitors
- Other NSAIDs/COX-2 inhibitors coded by WHODDE
- Non-biologic DMARDs
- Other non-biologic DMARDs coded by WHODDE
- Glucocorticoids
- Other glucocorticoids coded by WHODDE
- JAK inhibitors
- High potency opioids
- Systemic retinoids
- Phototherapy
- Inhaled marijuana
- Other treated coded by WHODDE

### 8.4.5 Inquiries for extra-musculoskeletal PsA manifestation

Inquiries for extra-musculoskeletal PsA manifestation will be listed by using the SAF.

## 8.4.6 Previous X-ray images of hands and feet

Previous X-ray images of hands and feet will be listed by using the SAF.

## 8.4.7 Prior and Concomitant Medications

Prior and concomitant medications will be summarized separately by WHODDE ATC level 2 and preferred name. Counts and percentages will be presented by treatment group using the SAF for Part A and Part A+B and using SAF-B for Part B. Prior medications will be summarized for Part A and concomitant medication will be summarized separately for Part A, Part B and Part A+B.

**Prior medications:** are defined as those medications with a start date and stop date prior to the first dose of study drug.

**Concomitant medications:**

- for part A, are defined as those medications with a start date on or after the first dose of study drug of part A but not after the first dose of Part B. A medication which started prior to first dose of part A and continued after first dose will also be considered as concomitant medications for part A.
- for part B, are defined as those medications with a start date on or after the first dose of study drug of part B. A medication which started prior to first dose of part B and continued after first dose of part B will also be considered as concomitant medications for part B.
- for part A+B, are defined as those medications with a start date on or after the first dose of study drug of part A. A medication which started prior to first dose of part A and continued after first dose will also be considered as concomitant medications for part A+B.

Details for imputing missing or partial start and/or stop dates of medication are described in [Section 7.3.2](#).

## 8.5 Extent of Exposure

Extent of exposure will be listed and summarized using the SAF separately for Part A and Part A+B and SAF-B for Part B.

For Part A+B, only two groups will be presented:

- Sonelokimab 120 mg,
- Sonelokimab 60 mg.

### 8.5.1 Treatment Duration

The duration (days) ([Section 7.1](#) for derivations) of exposure to study drug will be summarized using descriptive statistics by treatment group. In addition, the number of injections received will be summarized with count and percentages.

### 8.5.2 Treatment Compliance

Treatment compliance (See [Section 7.1](#) for derivations) will be summarized by treatment group using descriptive statistics. Counts and percentages will be provided using the following categories: <80%;  $80\% \leq x < 100\%$ ; 100%;  $100\% < x \leq 120\%$  and > 120%.

## 8.6 Efficacy Analyses

This section addresses the analyses to be conducted on the primary, secondary and exploratory efficacy variables.

### 8.6.1 Analysis Methods

#### 8.6.1.1 Logistic Regression Model

For the primary analysis, the hypotheses to be tested are that the proportion of participants who achieve ACR50 at Week 12 compared with baseline in the sonelokimab 120 mg Q2W, sonelokimab 60 mg Q2W or sonelokimab 60 mg Q4W arms are different from that of the placebo arm.

The logistic regression will be used to test the pairwise comparisons (placebo and either sonelokimab 120 mg Q2W, sonelokimab 60 mg Q2W, sonelokimab 60 mg Q4W or adalimumab) including fixed effects for treatment and the stratification factors (sex and exposure to biologic agents prior to the screening visit). Baseline score will also be included as a covariate where there is a single score for the endpoint, for example PASI for the analysis of PASI90.

Results will be presented in terms of number and percentage of responders, adjusted response rate, odds ratios (active/placebo), as well as risk difference (active-placebo), 95% CI, and estimated p-value.

The OR is a ratio of two odds, the odds of the event of interest in individuals exposed to active treatment and the odds of the event of interest in individuals exposed to placebo. The OR can be interpreted as:

- An  $OR=1$  indicates that the odds of having the event of interest (e.g. ACR50 responder) is the same in the active and placebo groups,
- An  $OR>1$  indicates that the odds of having the event of interest (e.g. ACR50 responder) is greater in active group than in the placebo group,
- An  $OR<1$  indicates that the odds of having the event of interest (e.g. ACR50 responder) is lower in active group than in the placebo group,

Using the procedure, the null hypothesis to be tested is that the OR is equal to one versus the OR is not equal to one.

In the case of having 0% or 100% response rate in one group, the estimated p-value (from a Fisher's Exact Test) will be presented, but the odds ratio and 95% CI will not be displayed.

The risk difference estimator will also be displayed and is derived from a logistic regression model. The adjusted response rates will be obtained from back transforming the estimates of the odds for each arm from the logistic regression model. The risk difference will be calculated as the difference (active-placebo) of the adjusted response rates. The delta method will be used to estimate the standard error of the risk difference from the logistic regression model (Ge et al. 2011). Appendix M has pseudo code used to create the logistic regression estimator approach.

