#### **12.3.2.1 Primary Analysis**

For the primary analysis, the hypotheses to be tested are that the proportion of participants who achieve ACR50 at Week 12 compared with baseline in the sonelokimab 120 mg Q2W, sonelokimab 60 mg Q2W, or sonelokimab 60 mg Q4W arms are different from that of the placebo arm.

Only the sonelokimab 120 mg Q2W, sonelokimab 60 mg Q2W, and sonelokimab 60 mg Q4W arms will be compared pairwise with placebo. A comparison among dose arms (sonelokimab 120 mg Q2W, sonelokimab 60 mg Q2W, and sonelokimab 60 mg Q4W) is not planned. [REDACTED]

A logistic regression model will be used to test the pairwise comparisons (placebo and either sonelokimab 120 mg Q2W, sonelokimab 60 mg Q2W, or sonelokimab 60 mg Q4W) including fixed effects for treatment and the stratification factors (sex and exposure to biologic agents prior to the Screening Visit). Results will be presented in terms of odds ratios, as well as risk difference, 95% CI, and estimated p-value.

For the primary analysis, a non-responder imputation method will be used. Participants will be considered non-responders to treatment if they discontinue the study prior to the Week 12 Visit due to any reason, have a missing ACR50 score at baseline or at the Week 12 Visit due to any reason, or take prohibited medication prior to the Week 12 Visit.

The sensitivity estimand for the primary endpoint will be analysis using a Generalized Linear Mixed Model (GLMM) to account for any missing data due to withdrawals for reasons other than lack of efficacy or taking prohibited medications. The model will include fixed effects for treatment, sex, prior biologic use, visit, treatment by visit interaction. The correlations between repeated measures will be modeled using an unstructured covariance matrix.

The primary analysis will be performed using the FAS.

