5.5 Sample Size and power

The sample size calculation is based on the primary efficacy endpoint (i.e., ACR50 response rate at Week 12 compared with baseline) with the primary comparisons of interest being:

sonelokimab 120 mg Q2W (Arm 1) vs placebo (Arm 4), sonelokimab 60 mg Q2W (Arm 2) vs placebo (Arm 4) and sonelokimab 60 mg Q4W (Arm 3) vs placebo (Arm 4) and determined based on assumed ACR50 response rates as follows:

- 40% with each sonelokimab dose regimen;
- 10% with placebo.

The estimated response rates for sample size were based on past IL-17 inhibitors for the treatment of participants with PsA. The Cosentyx FUTURE 2 study showed that ACR50 was achieved in 35% of secukinumab 300 mg and 37% of secukinumab 150 mg, vs 6% in the placebo arm [McInnes I.B. et al., 2015].

A sample size of n = 40 participants in each of the sonelokimab 120 mg Q2W, sonelokimab 60 mg Q2W, sonelokimab 60 mg Q4W and placebo arms (therefore, 160 participants in total) results in a power of more than 80%, while assuming an overall 2-sided alpha of 0.025, a placebo ACR50 response rate of 10% and a difference in ACR50 response rate of 30% between placebo and each sonelokimab dose regimen. An additional 40 participants will be randomized in the adalimumab arm. The adalimumab treatment will be used as an active reference arm, however, no formal comparison of sonelokimab or placebo vs adalimumab is planned.

Eligible participants will be randomized in a 1:1:1:1:1 ratio to sonelokimab 120 mg Q2W (Arm 1), sonelokimab 60 mg Q2W (Arm 2), sonelokimab 60 mg Q4W (Arm 3), placebo (Arm 4) or adalimumab 40 mg Q2W (Arm 5). The total proportion of participants with previous use of biologic agents will be capped at 30%.

Due to the use of the FAS with non-responder imputation, no accounting for dropout is required, therefore a total of approximately 200 participants will be randomized.

All calculations were performed in nQuery® Software version 8.5.1.0.

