#### **Primary Endpoints**

To adjust for multiple testing and to control the family-wise error rate, the Bonferroni-Holm method will be applied first to sonelokimab 120 mg Q2W (Arm 1) and sonelokimab 60 mg Q2W (Arm 2), followed by a step-down procedure to test for sonelokimab 60 mg Q4W (Arm 3).

The Bonferroni-Holm procedure will work as follows:

- 1) Let  $p_{\text{SLK120mg,Q2W}}$  and  $p_{\text{SLK60mg,Q2W}}$  be the p-value resulting from the comparison between sonelokimab 120 mg,Q2W vs placebo and sonelokimab 60 mg,Q2W vs placebo groups respectively.
- 2) If the smallest p-value obtained in step 1 is greater than or equal to  $\alpha/2 = 0.025$ , the procedure is stopped and no p-values are significant.
- 3) If the smallest p-value is declared significant (i.e p-value less than  $\alpha/2 = 0.025$ ), then compare the largest p-value with  $\alpha = 0.05$ . If the p-value is less than 0.05, then declared as significant. Otherwise not significant.
- 4) If both  $p_{\text{SLK120mg,Q2W}}$  and  $p_{\text{SLK60mg,Q2W}}$  are significant then the testing procedure will continue with the key secondary endpoints. The Bonferroni-Holm procedure used for the primary endpoint will be applied to each key secondary endpoint sequentially.
- 5) If the procedure passes all the key secondary endpoints for both doses (Arm 1 and Arm 2), then sonelokimab 60 mg Q4W (Arm 3) will be compared to  $\alpha = 0.05$  first for the primary endpoint and then sequentially through the key secondary endpoints.

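### The ACR50 and ACR20 models adjust for no baseline disease value and so may give up some power; prespecifying baseline DAPSA is an optional, low-cost improvement

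*Combined protocol and SAP*

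**What the plan says.** Protocol 12.3.2.1 describes the primary pairwise logistic model as "including fixed effects for treatment and the stratification factors (sex and exposure to biologic agents prior to the Screening Visit". SAP 8.6.1.1 keeps those terms and adds one rule: "Baseline score will also be included as a covariate where there is a single score for the endpoint". Its example is PASI for PASI90.

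SAP 8.6.2.1 defines ACR50 from TJC68, SJC66 and three of five further variables, so the rule adds nothing to that model. SAP 8.6.3.1 analyses ACR20 by the ACR50 methods. The model-based sensitivity analyses of ACR50 keep the primary covariates.

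Baseline values are used elsewhere. They enter the MMRM (SAP 8.6.1.2), which also serves the ACR components, and the multiple-imputation model (SAP 8.6.1.3). The baseline table in SAP 8.4.2 lists all seven ACR components and also "Baseline DAPSA", a single activity score.

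On power, SAP 5.5 gives "A sample size of n = 40 participants in each of" the three sonelokimab arms and placebo, and says that this "results in a power of more than 80" percent, "while assuming an overall 2-sided alpha of 0.025, a placebo ACR50 response rate of 10" percent and "40% with each sonelokimab dose regimen".

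**The concern.** The only visible reason for leaving baseline disease activity out of the ACR models is that ACR has no score of its own. Yet a single baseline activity score is already planned for tabulation. PASI90 and the continuous endpoints are adjusted for baseline, while the primary endpoint is not.

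The primary comparison also has little slack. In SAP 8.6.1.4 the smaller of the two Q2W p-values is tested at 0.025; if it passes, the instruction is "then compare the largest p-value with" 0.05. Both Q2W arms must succeed on ACR50 before any key secondary endpoint is tested, and both must clear the key secondary endpoints before the 60 mg Q4W arm is tested. A covariate measured before treatment that predicts response would raise the chance of passing that first step.

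**Working it through.** **Inputs.** From SAP 5.5: n = 40 per arm, ACR50 10% on placebo and 40% on each sonelokimab regimen, two-sided alpha 0.025. From SAP 8.6.1.1: covariates treatment, sex and prior biologic exposure, with Fisher's exact p-value if one group has 0% or 100% response. Not in the documents, and therefore varied: the association between baseline activity and ACR50 response.

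**Step 1: reproduce the stated power.** Pooled normal approximation:
- mean rate (0.10 + 0.40)/2 = 0.25
- null SE = √(2 × 0.25 × 0.75/40) = 0.0968
- alternative SE = √((0.10 × 0.90 + 0.40 × 0.60)/40) = 0.0908
- critical value for two-sided 0.025: 2.241
- power = Φ((0.30 − 2.241 × 0.0968)/0.0908) = Φ(0.914) = 82.0%

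Exact enumeration of the uncorrected chi-square test gives 83.3%. The plan's statement of more than 80% is reproduced.

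**Step 2: power of the planned logistic test, without and with one baseline covariate.** Trials were simulated with marginal rates fixed at 10% and 40%, and with one standard normal covariate of assumed strength.

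| Assumed log odds ratio per SD | Wald test only | With the SAP's Fisher fallback |
|---|---|---|
| 0 | 79.7% → 79.8% | 81.3% → 81.3% |
| 0.3 | 79.4% → 79.6% | not run |
| 0.5 (odds ratio 1.65) | 78.8% → 80.6% | 80.8% → 81.7% |
| 0.8 (odds ratio 2.23) | 79.2% → 83.1% | not run |
| 1.0 (odds ratio 2.72) | 79.3% → 84.5% | 80.1% → 85.7% |

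Monte Carlo error is about 0.5 points at 6,000 trials: √(0.81 × 0.19/6,000) = 0.0051. The right-hand column follows the SAP. Trials with no placebo responders occur with probability 0.9^40 = 1.5%, and a Wald-only calculation misses rejections there, which accounts for most of the gap between the columns.

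A separate simulation on the odds-ratio scale agrees on the gain: 79.8% → 79.7% at odds ratio 1.0, 80.4% → 81.5% at 1.5, 81.4% → 83.6% at 2.0 and 80.7% → 86.4% at 3.0. It counted about 1.5% of fits that did not converge as non-rejections, so its levels are slightly low.

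**Step 3: downside checks.**
- Expected responders per pair: 40 × 0.10 + 40 × 0.40 = 20. Responders per model term fall from 20/3 = 6.7 to 20/4 = 5.
- A skewed covariate gives similar gains and loses at most about 0.4 points if uninformative. Five uninformative covariates cost about 1 point (80.0% → 78.9%), so one is the sensible number.
- With both rates at 10%, rejection at nominal 0.05 stayed at or below 2.6% with the covariate, so there was no inflation.
- The variance of the standardised risk difference changes by +1% to −11% over the assumed range.
- The true marginal odds ratio is (0.40/0.60)/(0.10/0.90) = 6.0. The median fitted odds ratio moves from 6.5 to 9.5 when a covariate with log odds ratio 1.0 is added, and from 6.55 to 6.78 when the covariate is irrelevant.

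**ACR20.** The documents assume no ACR20 rates. At assumed rates of 20% and 55%, the gain is about 0 to 4 points.

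**The case against.** The case for leaving the plan alone is substantial:

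- The model is prespecified alike in protocol and SAP, adjusts for both stratification factors and reaches its stated power. The 0.025 test is also only the first Holm step: the chance that at least one Q2W arm passes it is about 92% to 93% without any baseline covariate.
- Nothing in the documents links a baseline value to ACR50 response. ACR50 is a percent improvement from each participant's own baseline, so a strong association cannot be presumed.
- Odds ratios are non-collapsible. Adding a prognostic covariate changes what the reported odds ratio means, so it is too strong to say that the adjustment leaves the reported result untouched.
- DAPSA is one choice among several, such as a joint count, HAQ-DI or hs-CRP. Its derivation section is listed in the SAP contents, but the text is not in the public copy.
- The subgroup models in SAP 8.10 already carry subgroup and interaction terms. A further covariate was not tested there.

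All of this stands as a limit on the claim. None of it defeats the suggestion: the cost of one uninformative covariate is close to nil even when it is skewed, and the gain is several points if the covariate is strongly prognostic. DAPSA has a practical argument: it is a single score, already planned for tabulation, which is what the SAP's own rule looks for.

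Two stronger readings are tempting. One is that the planned test falls short of 80%; with the SAP's Fisher rule applied it does not. The other is that power is certainly being lost; that needs a prognostic strength that the documents do not give.

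**Conclusion.** The ACR50 and ACR20 models omit baseline disease activity because of the single-score rule, and may give up some power as a result. This is an efficiency improvement of low priority. The planned analysis is valid and delivers about 81% power for the Wald test with the Fisher fallback.

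One baseline activity covariate would change power by about 0 points if uninformative, +1 to +2 points at a log odds ratio of 0.5 per SD (+0.9 with the fallback, +1.8 Wald only), and about +5 to +6 points at 1.0 (+5.6 and +5.2). These figures rest on the planned rates of 10% and 40%, full use of 40 per arm, sex and prior biologic use treated as given covariates, and an assumed prognostic strength. Where DAPSA would fall in that range cannot be settled from the documents.

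**What to change.** In SAP 8.6.1.1, prespecify baseline DAPSA as one continuous covariate in the ACR50 and ACR20 main models and in the sensitivity models that share their covariates. Leave PASI90 (which already has baseline PASI) and the SAP 8.10 subgroup models as they are. Keep the Fisher fallback.

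Replace a missing baseline DAPSA by the overall mean across arms. Under SAP 7.3.1 a participant with missing baseline data still counts as a non-responder, and a missing covariate would otherwise drop that FAS member from the model.

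State that the odds ratio is conditional on baseline DAPSA, and that the risk difference, averaged over participants' covariate values, is the population-level effect. SAP 9 already describes the risk-difference estimator in those terms; check that the Appendix M code, which is not in the public copy, averages in this way.

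Record the change in SAP 9 before the Week 12 unblinding. The cost is a few sentences and one model term. The downside is one more parameter with about 20 expected responders per comparison, and an odds ratio that will typically lie further from 1. If the sponsor prefers the present model, one line giving the reason would close the point.

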## 8.6.1.2 Mixed Model Repeated Measures

Continuous efficacy endpoints assessed over time will be analyzed using an MMRM model including treatment arm, baseline, visit, sex, prior exposure to biologic agents and treatment by visit interaction as fixed effects and participant as random effect. An unstructured covariance matrix will be used for the MMRM analysis, unless the model does not converge, in which case the covariance matrix (e.g. variance components, autoregressive, compound symmetry, and Toeplitz) will be decided upon model convergence status and the Akaike information criterion.

The MMRM will be used to test for differences in the mean of the endpoint of interest (e.g. change from baseline in TJC68) between groups of interest (e.g. each active treatment group versus placebo).

From the model, the adjusted least squares (LS) means in each group and the difference in LS means for the group comparisons will be estimated together with 95% CIs for the differences and p-values for the pairwise comparisons. Treatment effect estimates will be also extracted by visit.

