#### 12.3.3.2 Other Secondary Endpoints

For the other secondary endpoints, listed in Section 7.2.3, no confirmatory statistical testing will be performed, but statistical tests may be used for exploratory purposes only. All endpoints will be assessed at time points as outlined in the SOA in Section 3, Table 1, if not indicated otherwise.

All continuous endpoints will be summarized descriptively and analyzed using a mixed model for repeated measures (MMRM) including treatment arm, visit, sex, prior exposure to biologic agents and treatment by visit interaction as fixed effects. An unstructured covariance matrix will be used for the MMRM analysis, unless the model does not converge, in which case the covariance matrix will be decided upon model convergence status and the Akaike information criterion. The

least-squares means in each arm, the least-squares mean difference between arms, and its 95% CIs and p-values will be estimated by the model. Treatment effect estimates will be also extracted by visit.

All dichotomous endpoints will be summarized descriptively and analyzed using logistic regression with odds ratios, as well as risk difference and associated 95% CIs and p-values.

For dichotomous endpoints, a non-responder imputation method will be done and details will be defined in the SAP. For continuous endpoints, no imputation is planned.

FAS will be used for all other secondary endpoints analysis.

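### The SAP's MMRM adds a redundant participant random effect to an unstructured covariance, and its fallback names only equal-variance structures, so by-visit standard errors can be wrong if the fallback is used

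*Combined protocol and SAP*

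**What the plan says.** SAP 8.6.1.2 sets out the MMRM for continuous efficacy endpoints. Its list of model terms ends, and its covariance rule begins, with "treatment by visit interaction as fixed effects and participant as random effect. An unstructured covariance matrix will be used for the MMRM analysis". If there is no convergence, the structure is chosen by convergence status and AIC, with four examples: "e.g. variance components, autoregressive, compound symmetry, and Toeplitz". The same section requires 95% CIs and p-values for the pairwise comparisons, and adds: "Treatment effect estimates will be also extracted by visit".

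Protocol 12.3.3.2 lists "treatment arm, visit, sex, prior exposure to biologic agents and treatment by visit interaction as fixed effects". It has the same unstructured-first rule and the same open choice by convergence and AIC, but no participant random effect and no named fallback structures.

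SAP section 9 records changes from the protocol, down to the BASDAI derivation. It does not mention the added random effect.

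**The concern.** An unstructured residual matrix already allows any variance at each visit and any covariance between visits. A random participant intercept adds the same constant to every element of that matrix, so it contributes nothing that can be estimated separately. A program that follows the text literally is asked to estimate a parameter the data cannot identify. A non-converged fit or a singular Hessian is a foreseeable result, and non-convergence is exactly what triggers the fallback.

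The four named fallback structures, taken under their plain names, each assume one variance for all visits. AIC can rank them against each other, but it cannot bring in unequal variances if no such candidate is in the set. At stake are the intervals and p-values at each visit, including Week 12, for exploratory endpoints that will be reported at two-sided 0.05.

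**Working it through.** **Plan's own figure.** The documents give no power figure and no SD by visit for any continuous endpoint. The only power statement is for ACR50: 40 per arm, 10% versus 40%, two-sided alpha 0.025, power above 80%. With the pooled normal formula, SE under the null = √(2 × 0.25 × 0.75 / 40) = 0.0968, SE under the alternative = √((0.09 + 0.24) / 40) = 0.0908, and power = Φ((0.30 − 2.241 × 0.0968) / 0.0908) = 82.0%. The figure reproduces but has no bearing on the MMRM.

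**Inputs from the documents.**
- Model, first-choice covariance and fallback list: SAP 8.6.1.2.
- Part A post-baseline visits (SAP 7.2): Weeks 2, 4, 8 and 12 for the ACR components; Weeks 4, 8 and 12 for PsAID-12, BASDAI, LEI and SPARCC; Weeks 4 and 12 for SF-36v2 and FACIT-Fatigue; Week 12 only for mNAPSI.
- 40 participants per arm in five arms (SAP 5.5); two-sided alpha 0.05 (SAP 8.1).

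**Assumptions, not in the documents.** Residual SDs change linearly over visits, the ratio of Week 12 SD to first-visit SD runs from 0.8 to 2.0, the adjacent-visit correlation is 0.6, and data are complete.

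**Step 1: redundancy.** With K visits, an unstructured matrix R has K(K + 1)/2 parameters. Adding a random intercept gives V = R + σ²J, where J is a matrix of ones. For any constant c, the pair (R − cJ, σ² + c) gives the same V. At K = 4 there are 10 + 1 = 11 parameters, and a numerical check of the Jacobian gives rank 10.

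**Step 2: standard error under an equal-variance fallback.** The model's Week 12 standard error is close to one based on the root-mean-square (RMS) SD over visits, so

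q = model SE / true SE ≈ RMS SD / SD at Week 12, and type I error ≈ 2 × (1 − Φ(1.96 q)).

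For a ratio of 1.5, the SDs are 1, 1.167, 1.333 and 1.5. The mean square is (1 + 1.361 + 1.778 + 2.25) / 4 = 1.597, the RMS is 1.264, q = 1.264 / 1.5 = 0.843, and the type I error is 2 × (1 − Φ(1.651)) = 9.9%.

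The same calculation at four visits, with a null simulation (five arms of 40, 20,000 runs), gives:

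| Week 12 / first-visit SD | q | Large-sample error | Simulated, pooled variance | Simulated, unstructured |
|---|---|---|---|---|
| 0.8 | 1.13 | 2.7% | 2.6% | 4.8% |
| 1.0 | 1.00 | 5.0% | 4.9% | 5.0% |
| 1.25 | 0.90 | 7.7% | 7.6% | 5.0% |
| 1.5 | 0.84 | 9.9% | 9.6% | 4.9% |
| 2.0 | 0.77 | 13.0% | 13.0% | 5.0% |

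At the low end, SDs of 8, 8.5, 9 and 9.5 (ratio 1.19) give q = 8.768 / 9.5 = 0.923 and an error of 7.0%.

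**Step 3: does the choice of fallback matter?** Large-sample fits of variance components, compound symmetry, AR(1), AR(1) with a random intercept, and Toeplitz give q within 0.005 of each other at every ratio. With two or three visits, the error at ratio 2.0 is 12.1% to 12.8%.

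**Step 4: early visits.** The error runs the other way there. At ratio 1.5, q at the first visit is 1.264 and the type I error is 1.3%.

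**The case against.** The strongest reply is that the unstructured matrix remains the first choice. If the fit converges, for instance with the participant variance at zero, the marginal covariance is still unstructured and nothing changes. Harm needs both a fallback and unequal variances. The documents give no probability for the first, and 200 participants with four visits is not a hard case for ten covariance parameters. If 5% of fits fell back (assumed), a 9.9% conditional error would move the overall rate only to 0.95 × 5.0 + 0.05 × 9.9 = 5.2%. That stands: every error rate above is conditional on the fallback. Non-convergence is more plausible for LEI and SPARCC, which are modelled only in participants with a baseline score above zero.

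A reader might infer several stronger things that the documents do not support.
- **The SAP permits only equal-variance fallbacks.** The list is introduced as examples, so heterogeneous structures are not excluded; none is named.
- **Unstructured describes the single random effect, so the model is compound symmetry from the start.** The SAP ties the matrix to the MMRM analysis, and its autoregressive and Toeplitz alternatives make sense only across visits.
- **All continuous endpoints are affected.** The SAP's LDI section gives descriptive summaries only, and mNAPSI has one Part A visit, so there is nothing to pool. The four-visit figures match the ACR-component schedule. For hs-CRP, analysed on the log scale, any ratio refers to log values.
- **The Week 12 standard error is always too small.** It is too small only if the residual SD rises. The model adjusts for baseline, so the SD of raw change overstates the rise. With constant variance and a correlation with baseline falling from 0.8 to 0.5 (assumed), the ratio is √(1.0 / 0.4) = 1.58 for raw change but √(0.75 / 0.36) = 1.44 for residuals.
- **The null hypothesis changes.** It does not. The test is still of a mean difference at the visit; only its standard error is misspecified.

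**Conclusion.** The point holds in a limited form. The random effect is redundant, departs from the protocol without being listed, and can itself cause the failure that triggers the fallback. Given a fallback to any of the named structures, the Week 12 type I error is about 7% to 13% for assumed SD ratios of about 1.2 to 2.0, about 2.6% for a ratio of 0.8, and correct for a constant SD. The ratios are assumptions, because the documents give no SD by visit. If the unstructured fit converges, there is no effect.

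The scope is the MMRM analyses of continuous endpoints with two or more Part A visits. SAP 8.6.4 treats other secondary endpoints as exploratory, without confirmatory testing. ACR50, ACR20 and PASI90 use logistic regression, so no confirmatory error rate is affected. The change is still worth making: it is almost free and it prevents wrong by-visit intervals when the rule is followed as written.

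**What to change.** In SAP 8.6.1.2, delete the participant random effect. Model within-participant correlation only through an unstructured residual covariance with participant as the subject, as in protocol 12.3.3.2. The rest of the SAP's model, including its baseline covariate, can stay.

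Replace the open list with a fixed order for non-convergence: heterogeneous Toeplitz, then heterogeneous AR(1), then heterogeneous compound symmetry. If an equal-variance structure is still reached, use an empirical (sandwich) standard error, with a small-sample correction in the smaller subsets such as participants with LEI or SPARCC above zero at baseline. State in the report which structure was used for each endpoint.

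The cost is minor SAP wording and programming. Data collection and sample size do not change.
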